## Abstract

**Background:**

Prostate cancer is the second leading cause of cancer-related mortality in men worldwide. Prostate-specific membrane antigen (PSMA)–targeted radioligand therapy (RLT) has emerged as a theranostic strategy for metastatic castration-resistant prostate cancer (mCRPC), with [^177^Lu]Lu-PSMA-617 demonstrating survival benefits in the VISION trial. However, clinical responses are heterogeneous, and resistance mechanisms remain poorly understood. Liquid biopsy (LBx), particularly circulating tumor DNA (ctDNA), may provide a minimally invasive approach to assess tumor heterogeneity, monitor response, and detect emerging resistance.

**Objective:**

The LOOPS (Liquid Biopsy as a Biomarker in Patients Treated with PSMA Radioligand Therapy) study aims to prospectively investigate the prognostic and predictive value of ctDNA in patients undergoing PSMA RLT.

**Methods:**

LOOPS is a prospective, multicenter observational biomarker trial recruiting 100 patients with mCRPC eligible for PSMA RLT across 3 Bavarian cancer research centers in Germany. Patients will undergo up to 6 cycles of [^177^Lu]Lu-PSMA-617. Blood samples for ctDNA analysis will be collected longitudinally (at baseline and after cycles 1, 2, 4, and 6) and processed according to standardized protocols. Imaging with PSMA positron emission tomography–computed tomography and clinical and biochemical data will be systematically collected. The primary end points are the prognostic and predictive value of baseline ctDNA for treatment response, defined by imaging- and prostate-specific antigen (PSA)–based response criteria after 2 cycles of PSMA RLT. Predictive performance will be evaluated using receiver operating characteristic analyses, including the determination of optimal ctDNA cutoffs, sensitivity, specificity, positive and negative predictive values, and multivariable logistic regression models adjusting for relevant clinical confounders. Secondary end points assess the concordance and correlation between ctDNA dynamics, systematically assessed PSMA positron emission tomography–computed tomography response, and PSA changes, as well as associations between ctDNA and clinical or laboratory (eg, age, Gleason score, and other) characteristics at baseline and during follow-up. Exploratory analyses will investigate early molecular response patterns based on short-term ctDNA changes and will characterize clonal dynamics and potential resistance mechanisms under therapy.

**Results:**

The study has been funded by the German Research Foundation (Deutsche Forschungsgemeinschaft) since July 2025. Patient recruitment has already commenced, and in January 2026, a total of 63 patients have been enrolled. Analysis of LBx samples was initiated in January 2026, while recruitment and data collection are ongoing.

**Conclusions:**

The LOOPS study will provide the first prospective, systematic evaluation of ctDNA as a biomarker in PSMA RLT. By integrating molecular, imaging, and clinical data, it aims to clarify the role of LBx in response monitoring and the early identification of resistance. The results could pave the way toward personalized therapeutic strategies in mCRPC.

## Introduction

### Background

Prostate cancer is the second leading cause of cancer-related death in men worldwide [1]. Despite therapeutic advances, many patients progress to metastatic castration-resistant prostate cancer (mCRPC), a stage with limited therapeutic options and poor prognosis. Prostate-specific membrane antigen (PSMA) has emerged as a pivotal molecular target for imaging and therapy. PSMA expression is upregulated up to 1000-fold in prostate cancer cells and increases with tumor dedifferentiation, making it particularly relevant in mCRPC [2,3]. This biology enables theranostic strategies integrating molecular imaging and targeted radioligand therapy (RLT). The clinical implementation of PSMA-targeted RLT represents a significant therapeutic advance. [^177^Lu]Lu-PSMA-617, approved by the Food and Drug Administration and European Medicines Agency in 2022, demonstrated survival benefits in the pivotal VISION trial, prolonging both overall survival (15.3 vs 11.3 months; hazard ratio 0.62; *P*<.001) and radiographic progression-free survival (8.7 vs 3.4 months; hazard ratio 0.40; *P*<.001) compared to the standard of care alone [4].

### Unmet Need

Despite these advances, response heterogeneity and the ability to predict response remain major challenges. Only approximately 50% of patients achieved an objective radiographic response in the VISION trial [4]. This discordance between high PSMA expression on positron emission tomography (PET)–computed tomography (CT) and limited efficacy suggests incompletely understood resistance mechanisms, including tumor microenvironment heterogeneity, insufficient radiation doses to micrometastases, and intrinsic molecular factors such as genetic alterations in DNA damage repair pathways [5,6]. Liquid biopsy (LBx) has emerged as a promising tool that enables longitudinal, minimally invasive monitoring while mitigating the sampling bias of single-site tissue biopsies [7]. LBx analytes include circulating tumor cells (CTCs), circulating tumor DNA (ctDNA), extracellular vesicles, and tumor-derived RNA [8]. Among these, ctDNA is particularly promising in mCRPC. First, it is detectable in a substantial majority of patients (approximately 76%‐94%), with lower detection in patients with limited disease burden or low prostate-specific antigen (PSA) levels [9-11]. Second, ctDNA levels strongly correlate with clinical outcomes, including PSA response, progression-free survival, and overall survival, as demonstrated in multiple studies, including the TheraP trial [12,13]. Third, ctDNA provides a comprehensive view of the tumor genomic landscape, enabling detection of actionable mutations at higher rates than CTC-based assays or single-site tissue biopsies [14]. Recent studies have demonstrated specific genomic alterations detectable in ctDNA that predict resistance to PSMA RLT, including amplifications of *FGFR1* and *CCNE1*, as well as *CDK12* mutations [15]. Additionally, genome-wide copy number variation analysis has shown that a higher burden of genomic instability correlates with poorer treatment response [16]. Finally, ctDNA has been shown to correlate with imaging-derived biomarkers such as PSMA-positive tumor volume on PET, with correlations being particularly strong in patients with castration-resistant cancer (*r*=0.65; *P*<.001) compared to hormone-sensitive patients [11]. In contrast, early LBx applications in PSMA RLT using CTCs showed limited predictive value [17] and a 20% false-negative rate for PSMA expression [18].

Knowledge gaps remain regarding optimal ctDNA thresholds, the timing and magnitude of early on-treatment ctDNA dynamics that foretell radiographic progression, genomic correlates of resistance despite high PSMA expression, and the optimal timing for sampling. The LOOPS (Liquid Biopsy as a Biomarker in Patients Treated with PSMA Radioligand Therapy) trial is a multicenter, prospective biomarker trial in patients initiating PSMA RLT, designed to integrate serial ctDNA profiling with PSMA PET-CT, biochemical, and clinical end points to address the unmet need for predictive and prognostic biomarkers. The objectives are to assess whether baseline ctDNA tumor fraction and early ctDNA changes predict radiographic response, quantify the concordance between ctDNA burden and PSMA PET tumor volume, and identify ctDNA-detectable genomic alterations linked to resistance to PSMA RLT. To enhance analytical rigor, we will address clonal hematopoiesis (through paired leukocyte sequencing or bioinformatic filtering), standardize preanalytical handling, and report the assay limit of detection and reproducibility. By establishing fit-for-purpose ctDNA biomarkers, the LOOPS study (registered on August 11, 2025) aims to enable risk-adapted, personalized PSMA RLT in mCRPC. We hypothesize that baseline ctDNA burden and genomic features are prognostic for early nonprogression under [^177^Lu]Lu-PSMA-617 and that on-treatment ctDNA dynamics provide an early, quantitative readout of therapeutic efficacy that aligns with PSMA PET-CT, PSA responses, and clinical outcomes. Exploratory analyses address clonal evolution and resistance mechanisms emerging under the selective pressure of RLT.

## Methods

### Study Design

LOOPS is a prospective, multicenter, observational biomarker study embedded in routine care. No investigational treatment is introduced; rather, standard-of-care [^177^Lu]Lu-PSMA-617 is augmented by serial LBx sampling and centralized imaging reads.

### Study Setting

Three university hospitals within the Bavarian Cancer Research Center—Würzburg, Munich (Technical University of Munich [TUM] Klinikum), and Augsburg—participate. These centers collectively manage several hundred PSMA RLT cases annually, supporting feasibility and external validity.

### Eligibility Criteria

Adults (aged ≥18 years) with histologically confirmed prostate cancer that has progressed to mCRPC are eligible if they are candidates for PSMA RLT within approved indications, have previously received at least 1 androgen-receptor pathway inhibitor and 1 taxane-based chemotherapy, and have PSMA PET-CT within 8 weeks prior to cycle 1 demonstrating adequate target expression. Prior exposure to taxane-based chemotherapy is required as an inclusion criterion in accordance with regulatory approvals and the standard-of-care indication for PSMA-targeted RLT at the time of study design. This criterion ensures that all enrolled patients are treated within the approved clinical framework and reflects real-world treatment sequencing in mCRPC. Patients must provide written informed consent and must either be German speaking or have a translator available. Exclusion criteria are limited to the inability or unwillingness to adhere to study procedures and the absence of an interdisciplinary tumor board recommendation for PSMA RLT.

### Interventions

Therapy follows routine clinical practice: [^177^Lu]Lu-PSMA-617 is administered intravenously every 6 weeks for up to 6 cycles, with initiation, delay, or discontinuation at the discretion of the treating physician. The study does not modify dosing or scheduling.

### Outcomes

Two coprimary outcomes are specified. The first is the prognostic value of baseline ctDNA for nonprogression after 2 cycles, as assessed by PSA response according to PCWG3 (Prostate Cancer Clinical Trials Working Group 3) criteria [19]) and by RECIP 1.0 (Response Evaluation Criteria in PSMA-imaging, version 1.0) [20,21] defined as partial response or stable disease vs progression. The second is the concordance between ctDNA dynamics (percent change from baseline) and imaging-based response according to RECIP 1.0, as well as PSA response, after cycles 2, 4, and 6. Secondary outcomes examine associations between baseline ctDNA features and clinical or laboratory parameters (eg, age, Gleason score, PSA, alkaline phosphatase, lactate dehydrogenase, and metastatic distribution) and relate longitudinal ctDNA changes to clinical and laboratory trajectories. Exploratory outcomes include a very early molecular response defined a priori as a ≥30% decline in ctDNA at 6 weeks after the first cycle and the characterization of clonal dynamics and resistance-associated alterations across multiple time points.

### Participant Timeline

Participants are enrolled before cycle 1. Blood sampling for ctDNA occurs at baseline (≤14 days prior to cycle 1); before cycle 2 (approximately 6 weeks); and at imaging visits after cycle 2 (approximately 16 weeks), cycle 4 (approximately 28 weeks), and cycle 6 (approximately 40 weeks). An exploratory time point at 6 weeks after the first cycle enables the assessment of very early molecular response. PSMA PET-CT is obtained at baseline and after cycles 2, 4, and 6 and submitted for central review (Figure 1). All patients are treated with the approved PSMA RLT according to the manufacturer’s recommendations; accordingly, the treatment schedule and administered activity are fixed.

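### On the stated 6-weekly schedule, the visits labelled after cycle 2 and after cycle 4 (about weeks 16 and 28) fall after doses 3 and 5, and the text states no hold that would reconcile them

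*Protocol article*

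**What the plan says.** All references are to the protocol article.

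- **Dosing.** Under Interventions, the drug is "administered intravenously every 6 weeks for up to 6 cycles", "with initiation, delay, or discontinuation at the discretion of the treating physician". The same section says that the study leaves dose and timing alone. Participant Timeline concludes that "the treatment schedule and administered activity are fixed".
- **First on-treatment sample.** Participant Timeline puts it "before cycle 2 (approximately 6 weeks"). The Methods part of the abstract lists sampling "at baseline and after cycles 1, 2, 4, and 6", so the same draw is also called the one after cycle 1. Outcomes uses it for the exploratory early response, a "decline in ctDNA at 6 weeks after the first cycle".
- **Later visits.** Participant Timeline has blood drawn "at imaging visits after cycle 2 (approximately 16 weeks), cycle 4 (approximately 28 weeks), and cycle 6 (approximately 40 weeks"), and states that "PSMA PET-CT is obtained at baseline and after cycles 2, 4, and 6".
- **Use of these visits.** Under Outcomes, the first coprimary outcome is nonprogression after 2 cycles, judged by PSA and RECIP 1.0. The second is the agreement of ctDNA change with imaging and PSA response after cycles 2, 4 and 6. Sample Size, Statistical Methods and Results also tie the primary assessment to the second cycle.

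**The concern.** The dosing interval, the week of cycle 2 and the weeks of the restaging visits appear within two short sections, and they do not fit together. If doses are given every 6 weeks, a visit at week 16 is not a visit after two cycles, because the third dose was due at week 12.

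At stake is how many doses a patient has had when the primary scan, PSA and ctDNA sample are taken. Under the printed dosing interval, a site that follows the printed weeks would restage after three doses, while a site that follows the cycle label would restage after two. Three centres take part and 63 patients were enrolled by January 2026. Any such difference in practice would mix assessments made after different amounts of treatment and at different intervals from the last dose.

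**Working it through.** **Inputs.** Interval of 6 weeks, up to 6 cycles (Interventions). Cycle 2 at about week 6, so cycle 1 is week 0 (Participant Timeline). Stated visits at weeks 16, 28 and 40 (Participant Timeline).

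**Step 1: dose weeks.** Dose k falls at week 6(k − 1), which gives weeks 0, 6, 12, 18, 24 and 30.

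**Step 2: where a visit after cycle k belongs.** After dose k and before dose k + 1 means between week 6(k − 1) and week 6k. The stated week 6 for the sample after cycle 1 is reproduced (6 × 1 = 6). The other three are not:

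| Visit label | Window (weeks) | Stated week | Stated week minus 6k | Doses given by then | Weeks since last dose |
|---|---|---|---|---|---|
| after cycle 2 | 6 to 12 | 16 | 4 | 3 | 16 − 12 = 4 |
| after cycle 4 | 18 to 24 | 28 | 4 | 5 | 28 − 24 = 4 |
| after cycle 6 | 30 to 36 | 40 | 4 | 6 | 40 − 30 = 10 |

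The last row shows the same offset but no conflict. There is no cycle 7, so week 40 is still after cycle 6.

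**Step 3: spacing.** 28 − 16 = 40 − 28 = 12 = 2 × 6 weeks. The later spacing agrees with 6-weekly dosing, so the 4 weeks enter once, before the first restaging.

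**Step 4: readings that might remove the mismatch.**

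- *Clock started at the baseline draw, up to 2 weeks earlier.* Dose 3 is at week 14, still before week 16.
- *Clock started 4 weeks earlier.* Doses 3 and 5 fall at weeks 16 and 28, which fits the visits, but cycle 2 moves to week 10 against the stated 6.
- *Interval of 7 weeks.* Dose 3 is at week 14, before week 16.
- *Interval of 8 weeks.* Cycle 2 moves to week 8, and dose 6 falls on week 40 itself.
- *One hold of d weeks before cycle 3.* Doses fall at 0, 6, 12 + d, 18 + d, 24 + d and 30 + d:

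| d | Week 16: doses / weeks since last | Week 28 | Week 40 |
|---|---|---|---|
| 0 | 3 / 4 | 5 / 4 | 6 / 10 |
| 1 | 3 / 3 | 5 / 3 | 6 / 9 |
| 2 | 3 / 2 | 5 / 2 | 6 / 8 |
| 3 | 3 / 1 | 5 / 1 | 6 / 7 |
| 4 | 2 / 10 | 4 / 6 | 6 / 6 |

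For d = 4 the visits at weeks 16 and 28 are taken just before doses 3 and 5. Only a hold of about 4 weeks or more makes the labels true.

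**Step 5: dates, supportive only.** Results expects recruitment to finish in September 2026 and every restaging after cycle 2 to be done by the end of 2026. If cycle 1 is on 30 September 2026, week 12 (84 days) is 23 December 2026 and week 16 (112 days) is 20 January 2027. Week 16 stays within 2026 only for cycle 1 up to 10 September (10 September + 112 days = 31 December).

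**The case against.** The strongest reply is that the cycle, not the week, is the operative anchor. Every restaging-based end point is worded by cycle. The weeks 16, 28 and 40 appear once, in brackets and marked as approximate. The one outcome defined by a week, the 6-week molecular response, is untouched. The week figures also cohere with each other if routine practice pauses for restaging before cycle 3, and treatment timing is left to the physician. Figure 1 might show such a pause.

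Much of this stands, and it rules out three stronger readings that a reader might infer:

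- *That the primary end point is undefined.* It is not, because the labels point consistently to an assessment before dose 3.
- *That weeks 16, 28 and 40 are a miscalculation.* The documents cannot show this; an unstated pause would explain them equally well.
- *That all three visits conflict with dosing.* Only weeks 16 and 28 do.

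The date check is weak as well, since it depends on when in September the last patients start.

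What does not stand is that the wording is harmless. An offset of 0 at cycle 1 and exactly 4 weeks at each later visit is systematic, and 4 weeks is two thirds of a cycle, so approximation does not explain it. Discretionary delay covers individual patients. It is not a planned hold for everyone, and it sits badly with a schedule described as fixed. If Figure 1 does show a pause, the text of Interventions and Participant Timeline would still disagree with it.

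**Conclusion.** The point holds in limited form and should be fixed. Taken as printed, the schedule puts the visits labelled after cycle 2 and after cycle 4 one dose too late, each 4 weeks after the next administration. Week 40 shows the same offset without consequence for the dose count. These visits supply the coprimary outcomes, so this is more than a clerical matter. The cycle labels are nevertheless most likely what is meant, and the remaining uncertainty is whether restaging before dose 3 is planned for about week 12 or, after a hold, about week 16.

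The conclusion assumes that week 0 is cycle 1, as the stated week of cycle 2 implies, and that doses run every 6 weeks as stated. It concerns the text only, because Figure 1 is not shown. Nothing in the documents indicates that any patient has in fact been restaged after a third dose. Sample size and power do not depend on this point.

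**What to change.** 1. State that the scan, PSA and ctDNA sample for restaging after 2 and after 4 cycles are taken before the third and fifth administrations. This is needed whichever weeks are right.
2. Establish what the three centres actually do, then make the text agree. If dosing runs on without a break, change the visits to about weeks 12, 24 and 36. If there is a restaging pause, state a hold of cycle 3 until about week 16, and amend both the 6-weekly interval in Interventions and the description of the schedule as fixed in Participant Timeline. Changing the weeks without this check could introduce a new error.
3. Use the cycle data already captured under Clinical Data to identify any restaging done after a further dose.

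The cost is wording in Interventions and Participant Timeline. No extra data collection, visits or patients are needed.

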**Figure 1. F1:**
[figure not shown]
Time points of blood sampling for liquid biopsy in the LOOPS (Liquid Biopsy as a Biomarker in Patients Treated with Prostate-Specific Membrane Antigen Radioligand Therapy) study. PET: positron emission tomography.

### Sample Size

The planned sample size of 100 patients is based on a priori biometrical considerations and reflects expected feasibility in this population with advanced mCRPC. Due to disease severity and anticipated attrition, the primary end point (treatment response at first posttherapy restaging after 2 cycles of therapy) is expected to be evaluable in approximately 70 patients. On the basis of this effective sample size, power calculations demonstrate that clinically meaningful differences in response rates between patients with and without a ctDNA-based predictive marker or marker change can be detected with 80% power at a 2-sided significance level of α=.05. Specifically, depending on the prevalence of the marker or marker change (25%, 50%, or 75%), differences in response probabilities of 0.33 to 0.41 between marker-positive and marker-negative patients are detectable using Fisher exact test. These effect sizes correspond to sensitivities ranging from 38% to 88% and specificities from 44% to 93%, supporting the ability of the study to evaluate the prognostic and predictive performance of ctDNA metrics. Therefore, the planned sample size is considered adequate for the primary analyses while remaining consistent with the pragmatic, multicenter, observational design of the study. To control the family-wise error rate for the 2 coprimary end points, a hierarchical testing strategy will be applied. The association between baseline ctDNA and treatment response will first be tested at a 2-sided significance level of α=.05. Only if this test is statistically significant, the discriminative performance (receiver operating characteristic analysis and area under the curve) will be formally evaluated at the same α level.

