### Limitations and Challenges

Several methodological challenges must be acknowledged. First, ctDNA detection is not uniform across all patients. Low-shedding tumors or those with limited tumor burden may yield false-negative results. Comparative studies have shown that ctDNA detection rates are significantly lower than PSMA PET detection rates, particularly in hormone-sensitive disease and at low PSA levels [11]. Although LOOPS uses sensitive sequencing and harmonized SOPs, residual variability in detection and quantification is unavoidable.

Second, ctDNA is a systemic signal and cannot localize alterations to specific lesions, potentially obscuring intrapatient heterogeneity evident on PET-CT. Consequently, lesion-restricted resistance mechanisms can be systemically diluted below detection thresholds. This underscores the value of integrating molecular and imaging biomarkers rather than privileging either alone.

Third, attrition is expected in an advanced disease cohort; although the analysis plan anticipates approximately 70 evaluable patients for the primary end point, small numbers in exploratory subgroups will limit power and mandate cautious interpretation with appropriate multiplicity control. However, experience from smaller pilot studies suggests that meaningful associations can be detected even in cohorts of 17 to 44 patients [15,16], providing confidence in the planned sample size.

Fourth, generalizability may be constrained by recruitment within 3 Bavarian academic centers and by variation in locally available PSMA-directed radiotracers; central reading and SOP harmonization mitigate, but do not eliminate, site-level heterogeneity.

Fifth, as an observational study embedded in routine care, LOOPS cannot establish causal effects or test treatment adaptation; early-change analyses will use landmarking to reduce immortal time bias; however, residual confounding may persist.

Sixth, posttherapeutic single-photon emission CT–based dosimetry is not included in the analysis. Although absorbed radiation dose is a biologically relevant determinant of treatment response and resistance, homogeneous dosimetric data are not available due to heterogeneous clinical imaging protocols across the participating centers and the current lack of standardized dosimetry methodologies.

Finally, despite paired leukocyte filtering, clonal hematopoiesis and preanalytical factors remain potential sources of noise.

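### The primary end point exists only at the post-cycle-2 restaging, and no rule classes death or documented progression before it, so a partly disease-related 30% loss can bias the main estimates

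*Protocol article*

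**What the plan says.** Sample Size enrols 100 patients and foresees a usable outcome in roughly 70 of them, in a sentence that opens: "Due to disease severity and anticipated attrition, the primary end point (treatment response at first posttherapy restaging after 2 cycles of therapy) is expected". The power statement then rests on those 70: "On the basis of this effective sample size, power calculations demonstrate" that "differences in response probabilities of 0.33 to 0.41 between marker-positive and marker-negative patients are detectable using Fisher exact test", at 80% power and two-sided α of 0.05.

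Outcomes gives the first coprimary outcome as nonprogression after two cycles by PSA (PCWG3) and RECIP 1.0, "defined as partial response or stable disease vs progression". Participant Timeline puts the restaging visit at about 16 weeks. Under Interventions, the treating physician may delay or stop therapy before then.

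Statistical Methods names missing-data handling and sensitivity analyses in general terms. Limitations and Challenges says that "attrition is expected in an advanced disease cohort" and takes this up as a question of small numbers, power and multiplicity. Bias from selection into the evaluable set is not mentioned.

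**The concern.** The marker is read at baseline, when nobody knows who will reach restaging. The outcome is read only in those who do. Disease severity is one of the two reasons given for non-evaluability, so some of the missing 30 will have died or progressed first. For an outcome called nonprogression, those patients are failures rather than missing observations. If the plan counted them as progression they would be evaluable, and severity could not be a reason for losing them.

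The loss may also be related to the marker. The article's Unmet Need section says that ctDNA levels correlate strongly with progression-free and overall survival, so early failures are likely to include more patients with high ctDNA.

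At stake are the quantities that Statistical Methods lists as primary outputs: cutoffs, sensitivity, predictive values and the adjusted association. Estimated in those who reach restaging, they would describe a group that cannot be identified when the test is used.

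**Working it through.** **1. The plan's own figure.** Inputs from Sample Size: 70 evaluable, Fisher exact test, 80% power, two-sided α = 0.05, marker prevalence 25%, 50% or 75%. The response rate in marker-negative patients is not given; 0.3 to 0.5 was assumed. By exact enumeration, the smallest detectable difference is about 0.33 (35 vs 35, marker-negative rate 0.5; power at 0.33 is 0.795). It rises to about 0.41 (unequal split, marker-negative rate 0.3, doubled one-tail p-value; power at 0.41 is 0.79 to 0.81). The stated 0.33 to 0.41 is reproduced, and 70 / (1 − 0.30) = 100. The arithmetic is sound and does rest on 70 patients.

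**2. What loss can do to a true difference of 0.33.** The following inputs are assumptions, not document figures: 100 patients, 50 with high ctDNA, true nonprogression 38% (high) and 71% (low). Expected counts are:

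- High ctDNA: 31 progress, 19 do not.
- Low ctDNA: 14.5 progress, 35.5 do not.

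With high ctDNA as the test for progression:

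- difference = 0.71 − 0.38 = 0.33
- odds ratio = (31 × 35.5) / (19 × 14.5) = 4.0
- sensitivity = 31 / 45.5 = 0.68
- specificity = 35.5 / 54.5 = 0.65
- PPV = 31 / 50 = 0.62
- NPV = 35.5 / 50 = 0.71
- nonprogression = 54.5 / 100 = 0.545

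Four assumed loss patterns, each leaving about 70:

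- A: 60% of progressors and 7% of nonprogressors lost, regardless of ctDNA.
- B: progressors lost 70% (high) and 30% (low); nonprogressors 10%.
- C: progressors lost 40% (high) and 30% (low); nonprogressors 25%.
- D: progressors lost 50%; nonprogressors lost 30% (high) and 10% (low).

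| | Truth | A | B | C | D |
|---|---|---|---|---|---|
| Evaluable | 100 | 68.9 | 68.5 | 69.6 | 68.0 |
| Progressors among the lost | – | 88% | 83% | 55% | 71% |
| Nonprogression | 0.55 | 0.74 | 0.72 | 0.59 | 0.67 |
| Difference | 0.33 | 0.26 | 0.11 | 0.29 | 0.35 |
| Odds ratio | 4.0 | 4.0 | 1.7 | 3.4 | 5.1 |
| Sensitivity | 0.68 | 0.68 | 0.48 | 0.65 | 0.68 |
| Specificity | 0.65 | 0.65 | 0.65 | 0.65 | 0.71 |
| PPV | 0.62 | 0.41 | 0.35 | 0.57 | 0.54 |
| NPV | 0.71 | 0.85 | 0.76 | 0.72 | 0.82 |

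Example, pattern B: retained progressors are 31 × 0.3 = 9.3 and 14.5 × 0.7 = 10.15; retained nonprogressors are 19 × 0.9 = 17.1 and 35.5 × 0.9 = 31.95. The difference is 31.95/42.1 − 17.1/26.4 = 0.76 − 0.65 = 0.11, and the odds ratio is (9.3 × 31.95) / (17.1 × 10.15) = 1.7.

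At this single cutoff the AUC is (sensitivity + specificity)/2: 0.67 in truth and under A, 0.56 under B, 0.65 under C, 0.69 under D.

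**3. Reading the table.** Loss that depends on outcome alone (A) moves the nonprogression rate, PPV, NPV and difference, but not the odds ratio, sensitivity or specificity. When loss also depends on ctDNA among progressors (B, C), sensitivity, odds ratio and AUC fall too. Specificity moves only when loss among nonprogressors depends on ctDNA (D).

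**4. The same question from the evaluable side.** Suppose the 70 evaluable show nonprogression of 32% (high) and 68% (low), a difference of 0.36, and all 30 others are counted as progression. With a share s of the 30 in the high group of 50, the rates become (50 − 30s) × 0.32/50 and (50 − 30(1 − s)) × 0.68/50. For s = 0.5, 0.6, 0.7 and 0.8 the difference is 0.25, 0.31, 0.37 and 0.43. Fisher power is 0.69, 0.88, 0.97 and 0.99, against 0.79 to 0.82 in the evaluable set. Overall nonprogression drops from 50–55% to 35–38%.

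**The case against.** The article nowhere says that patients who fail before restaging are excluded. Seventy is a projection used for sizing, the text mentions missing-data handling, and an analysis plan that is not shown may contain the rule. PSA is part of the outcome and could classify some patients without a scan. Two causes of loss are named with no split between them, so not all 30 need be early failures.

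Most of this stands as a limit on the claim. A reader might infer that the plan drops its worst early failures, and that every primary estimate is thereby biased toward no effect. The documents do not support that. Exclusion is an inference, though a fair one, because patients counted as progression would not be non-evaluable. Specificity is unchanged in patterns A to C, and the odds ratio and sensitivity are unchanged in A. Pattern D moves the association upward. The large shifts in A and B assume that 83 to 88% of the losses are progressors; with 55% (C) the difference falls only to 0.29.

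The objection does not remove the point. What is criticised is what the article fixes: an end point tied to restaging, a set of 70 reduced partly by disease severity, and a limitations section that considers power only. General missing-data language does not settle it, since death from disease before restaging is an outcome. PSA may rescue some patients, but Sample Size still ties the end point to restaging.

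**Conclusion.** The concern holds as a risk of selection bias in the primary analysis, of unknown size. As written, the outcome has no place for death or documented progression before about week 16, while about 30 of 100 patients are expected to be non-evaluable, partly because of disease severity. Restricting the analysis to the rest can bias the nonprogression rate, PPV, NPV and risk difference. If loss also depends on ctDNA, it can bias the odds ratio, sensitivity and AUC. Specificity at a fixed cutoff is safe unless loss among nonprogressors depends on ctDNA.

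Under the assumed patterns a true difference of 0.33 would be seen as anything from about 0.11 to 0.35. Attenuation is the more plausible direction, given the link between ctDNA and survival that the article cites, but it is not established. The range rests on an assumed even marker split, assumed true rates and assumed loss fractions. The sample-size arithmetic itself is not in question.

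**What to change.** Define the first coprimary outcome for all patients who start cycle 1. Count as progression any of the following before the post-cycle-2 restaging: death from disease; documented clinical, PSA or radiographic progression; or stopping for documented progression. Treat losses unrelated to disease, such as a move or withdrawn consent, as missing, handled for example by multiple imputation using baseline ctDNA, PSA, LDH and ALP. Keep the restaging-evaluable analysis as a sensitivity analysis, report the baseline ctDNA of patients who do not reach restaging, and name the selection bias in the limitations. Fix the rule before ctDNA results are linked to outcome; recruitment is planned to run to September 2026.

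Cost: the end point becomes a composite, and its clinical component is less standardised than a central PET read, the more so because stopping is at the physician's discretion. The reason and date of stopping must be captured; Clinical Data lists cycles administered but neither of these. No extra patients are needed. More power is not guaranteed: in the step 4 illustration it falls to 0.69 if only half of the early failures have high ctDNA.
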